## 2.6 Exploratory endpoints

The exploratory endpoints of the study include the following:

- extent and duration of SARS-CoV-2 viral shedding, as evaluated with PCR testing of nasopharyngeal swab samples;
- extent and time course of SARS-CoV-2 virus-specific antibody responses in serum;
- possible other biomarker changes in blood in study subjects.

# 3 STUDY DESIGN

## 3.1 Type and design of the study

This is a phase 2, placebo-controlled, double-blind, randomized, parallel-group treatment trial, performed at several study sites in a primary public health care setting. The study will be started in the region of Satakunta in Finland, but it may be expanded to other regions of Finland. Up to 600 evaluable subjects are planned to participate in the trial. The subjects will be randomized to receive either either HCQ capsules at 300 mg b.i.d. for one day and then 200 mg b.i.d. for 6 days, or placebo capsules for 7 days.

## 3.2 Randomization and blinding

This is a double-blind study. The participants and study personnel will remain blinded to the treatment allocation by having both investigational medicinal products (IMPs) packed in identical containers. Masking of the treatments is performed by re-

formulation of the IMPs so that the HCQ capsules and the placebo capsules have identical appearance.

At the screening visit, subjects who have signed the informed consent form (ICF) will be given screening numbers beginning from S1001. Randomization will be performed when the investigator has confirmed a subject's eligibility. After randomization, subjects will receive subject numbers starting from 1001 and will be allocated to the treatment assigned to each subject number as indicated by the randomization scheme. Detailed information on randomization will be provided in a separate Randomization Plan/Request document prepared by the DM provider.

In case of a medical emergency, the treatment code may be opened in the electronic data management system of the study (Viedoc™). Unblinding by the investigator is restricted to situations when knowledge of the treatment allocation is considered necessary for the safety and medical treatment of the subject. The reason for unblinding will be documented, along with the date and time of unblinding and an identifier of the person who broke the code. In case of a subject's death or hospitalization, that subject's participation in the study is concluded, and the treatment code of that subject will be opened by the Medical Lead of the study. For hospitalized subjects, this information will be communicated to the hospital in charge of the patient's subsequent medical care. De-identified unblinded information on deaths and hospitalizations will also be provided to the SC for ongoing evaluation of the participants' safety.

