## 2.5 Secondary endpoints

The secondary endpoints of the study are:

- duration and severity of Covid-19-related symptoms, as reported by the participants in the form of daily self-assessments;
- number of Intensive Care Unit treatment episodes due to Covid-19 infection within four weeks of entry into the study;
- number of deaths due to Covid-19 infection within four weeks of entry into the study;
- number of hospitalizations due to Covid-19 infection within three months of entry into the study;
- number of Intensive Care Unit treatment episodes due to Covid-19 infection within three months of entry into the study;
- number of deaths due to Covid-19 infection within three months of entry into the study;
- number of treatment-related adverse events (AEs) and serious AEs (SAEs);
- number of participants with treatment-related AEs and SAEs;
- all-cause mortality within six months of entry into the study (including post-study follow-up of consenting participants);
- all-cause hospitalizations within six months of entry into the study (including post-study follow-up of consenting participants); and
- self-assessed symptoms of anxiety of the study participants, as assessed with repeated administration of the Generalized Anxiety Disorder 7-item Scale (GAD-7).

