The follow-up period will start at the 4-week visit and will last until 3 months after start of IMP intake. During the follow-up period, information on health care services that the subjects have received in public health care is collected from the Care Register for Health Care, and information on possible deaths is collected from death certificates archived by Statistics Finland. All subjects will be contacted by telephone 3 months after start of IMP intake for an interview on possible AEs and other health outcomes.

After the follow-up period, with the subject's consent, additional post-study follow-up information will be collected from the Care Register for Health Care and from death certificates until 6 months after start of IMP intake.

The study outline is presented in Table 1 below.

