#### 4.7 Withdrawal of subjects

A subject has the right to withdraw his/her consent without any need to justify this decision. However, efforts should be made to find out the reason of the withdrawal. Possible withdrawal will not have any negative effect on the subject's future medical care.

The investigator may withdraw a subject from the study at any time based on the investigator's clinical judgement. A subject will be withdrawn from further IMP dosing if he or she starts a prohibited medication, develops suspected severe or moderately severe pneumonia, requires treatment in hospital, or other inclusion and exclusion criteria are no longer met. A subject will also be withdrawn from further IMP administration if she/he fails to comply with the trial protocol, or an AE jeopardizing her/his well-being occurs, or if the discontinuation is otherwise in the best interest of the subject.

Subjects who discontinue the study drug prematurely will be encouraged to attend all study visits and complete all study assessments. Still, subjects will retain the right to withdraw their consent for the study, and no study procedures should be carried out against their will.

All information collected from a withdrawn subject, including the reason of withdrawal, will be included in the study file for use as study data and for purposes of verification.

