### 7.2 Assessment of efficacy

#### 7.2.1 Evaluation of patient records

The patient records will be evaluated, including information collected from health-related registers (the Care Register for Health Care and death certificates archived by Statistics Finland), until 6 months after start of IMP intake to determine the following endpoints:

- number of hospitalizations due to Covid-19 infection within four weeks of entry into the study;
- number of Intensive Care Unit treatment episodes due to Covid-19 infection within four weeks of entry into the study;
- number of deaths due to Covid-19 infection within four weeks of entry into the study;
- number of hospitalizations due to Covid-19 infection within three months of entry into the study;
- number of Intensive Care Unit treatment episodes due to Covid-19 infection within three months of entry into the study;
- number of deaths due to Covid-19 infection within three months of entry into the study;
- all-cause mortality within six months of entry into the study including post-study follow-up of consenting participants);
- all-cause hospitalizations within six months of entry into the study (including post-study follow-up of consenting participants).

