### 13 CRITERIA FOR PREMATURE STUDY TERMINATION

The study may be discontinued at the discretion of the Principal Investigator or the Sponsor based e.g. on the occurrence of the following:

- ADRs unknown to date in respect to their nature, severity, and duration or the unexpected incidence of known ADRs;
- New information becomes available that mandates study discontinuation, e.g. for futility or for proof of efficacy of HCQ or another type of treatment of Covid-19 infection in the patient population of this study.
- Other medical or ethical reasons affecting the continued performance of the study.
- Difficulties in the recruitment of subjects.
- Significant deviations from the study protocol.

The investigator will inform the EC and the Sponsor will inform the CA if the study is terminated prematurely. The Sponsor reserves the right to prematurely terminate the study for valid scientific or administrative reasons. The investigator will proceed to appropriate actions concerning the study subjects in the case of premature termination of the study.

A study site may withdraw from further subject recruitment at any time if sufficient resources can no longer be allocated to proper execution of the study procedures. Already enrolled subjects should be treated and followed up according to the study protocol even if a site is withdrawn from further enrollment activities.

Individual study subjects are free to withdraw from further study treatment and from further study procedures if they wish. In addition, subjects should be withdrawn by the investigator from further study medication in case the patient must be hospitalized for any reason, if the subject starts a prohibited medication or if an AE severe enough to justify discontinuation of treatment with HCQ develops. The investigator may withdraw a subject from the study at any time based on the investigator's clinical judgement. A subject will also be withdrawn from further IMP administration if she/he fails to comply with the trial protocol, or if the discontinuation is otherwise in the best interest of the subject.

Subjects who discontinue the study medication prematurely will be encouraged to attend all study visits and complete all study assessments.

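### Section 3.2 ends participation at any hospitalization, against Sections 3.3, 4.7, 6.3 and 13; taken literally it truncates symptom, GAD-7, visit and adverse event data, unequally by arm if HCQ works

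*Protocol*

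**What the plan says.** Section 3.2 sets one rule for death and hospitalization together: the subject's "participation in the study is concluded, and the treatment code of that subject will be opened by the Medical Lead of the study". It is not limited to Covid-19 admissions. For hospitalized subjects the allocation is then passed to the treating hospital.

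Other current sections treat the hospitalized subject differently:

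- **Section 4.7** lists need for hospital treatment among the reasons to stop study dosing. It then says: "Subjects who discontinue the study drug prematurely will be encouraged to attend all study visits and complete all study assessments".
- **Section 13** says that "subjects should be withdrawn by the investigator from further study medication in case the patient must be hospitalized for any reason", and repeats the encouragement to complete assessments.
- **Section 3.3** says: "All subjects will be contacted by telephone 3 months after start of IMP intake". Section 6.3 repeats this and makes that call the end of participation.
- **Section 7.2.1** evaluates patient records and registers "until 6 months after start of IMP intake to determine the following endpoints". The list covers hospitalization, ICU and death endpoints at 4 weeks, 3 months and 6 months, with no exception for hospitalized subjects.
- **Section 3.3** also provides, with consent, that "additional post-study follow-up information will be collected from the Care Register for Health Care and from death certificates until 6 months" after the start of study medication.

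**The concern.** A site with a newly admitted subject has two incompatible instructions: close the subject, or stop the medication and keep following. Sites may choose differently, and the choice decides which data exist.

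The data at stake need an active participant: the daily symptom self-assessments and GAD-7 (both secondary endpoints in Section 2.5), the samples at the 2- and 4-week visits, and adverse events. Closure falls on the sickest subjects and is triggered by the event that the trial is designed to reduce. If HCQ works, or harms, the amount of missing data differs by arm. An analysis plan cannot recover assessments that were never made.

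There is also a question for the primary endpoint. A first admission for another cause would close the subject under Section 3.2, and the protocol does not say that a later Covid-19 admission within four weeks still counts.

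**Working it through.** **Step 1. Which rule applies to an admitted subject?**

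| Section | Effect of hospitalization | Follow-up afterwards |
|---|---|---|
| 3.2 | Participation concluded, code opened | None stated, apart from reporting to the Steering Committee |
| 4.7 | Dosing stopped | Encouraged to complete all visits and assessments |
| 13 | Medication stopped, any cause of admission | Same encouragement |
| 3.3, 6.3 | No exception | All subjects telephoned at 3 months |
| 7.2.1 | No exception | Records and registers to 6 months |

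Section 3.2 is the only one that ends participation.

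**Step 2. Which data depend on participation?**

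- Daily symptom reports: first two weeks (Section 7.2.2). Lost from admission to day 14; an admission after day 14 loses none.
- GAD-7: 2- and 4-week visits (Section 7.2.2).
- PCR, antibody, biomarker, safety laboratory and HCQ samples: 2- and 4-week visits (Section 6.2).
- Adverse events: Section 7.3.3 gives the end of follow-up in one place and the end of study participation in another. The two diverge once Section 3.2 closes a subject early.
- Hospitalization, ICU and death endpoints, such as the "number of Intensive Care Unit treatment episodes due to Covid-19 infection within four weeks of entry into the study": from records and registers (Section 7.2.1), so they do not clearly depend on participation.

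**Step 3. How many subjects?**

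Inputs: placebo rates of 15%, 10% and 5% and a 50% risk reduction (Section 8.1); up to 600 subjects (Section 8.1); half exposed to HCQ (Section 10), hence 300 per arm.

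The planning rates are read correctly if they reproduce the stated group size. With p1 = 0.15, p2 = 0.075, mean 0.1125, two-sided 0.05 and 80% power:

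n = [1.960 × √(2 × 0.1125 × 0.8875) + 0.842 × √(0.15 × 0.85 + 0.075 × 0.925)]² / 0.075², which rounds up to 278 per group, as stated. The same formula gives 435 at 10% and 906 at 5%, also as stated. The sample size is not in dispute.

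Expected subjects closed = 300 × rate in each arm:

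| Placebo rate | Placebo | HCQ | Total | Share of 600 |
|---|---|---|---|---|
| 15% | 45 | 22.5 | 67.5 | 11.25% |
| 10% | 30 | 15 | 45 | 7.5% |
| 5% | 15 | 7.5 | 22.5 | 3.75% |

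These count Covid-19 admissions within four weeks only. Other admissions, and those up to 3 months, would add to them; the protocol gives no rate. The table counts closed subjects, not lost values: the loss on each item depends on the day of admission, which the protocol does not project.

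**The case against.** A reader might infer that the ICU, death, 3-month and 6-month endpoints are cut off in the very subjects who have those events. The documents do not support this. Section 7.2.1 takes these endpoints from records and registers without excepting hospitalized subjects. During follow-up, "information on health care services that the subjects have received in public health care is collected from the Care Register for Health Care". The 6-month collection is post-study by design, so the protocol itself separates ascertainment from participation. Hospitalization is also a serious adverse event, to be followed until resolved, chronic or stable (Section 7.3.3), and the Steering Committee follows all hospitalizations and deaths (Section 10). An estimate of deaths after closure would need an in-hospital mortality that the protocol does not give, and would not measure deaths lost.

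This answer is strong but incomplete. Section 3.3 places 3-month register collection in a follow-up period that starts at the 4-week visit, which a subject closed earlier does not reach. No sentence says that the collection in Section 7.2.1 survives closure under Section 3.2.

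Three narrower objections stand in part:

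- The encouragement in Sections 4.7 and 13 covers early discontinuation. Dosing lasts seven days, so a subject admitted after completing it is not addressed there. The conflict with the 3-month call to all subjects remains for that subject.
- Section 8.2.2 makes secondary evaluations mainly descriptive, which lowers the stakes but does not remove the bias in a comparison of arms.
- Data collected after admission may be unblinded, because the code is opened and sent to the hospital. This is a reason to flag them, not to forgo them.

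**Conclusion.** The protocol contradicts itself on whether a hospitalized subject stays in the study. Followed literally, Section 3.2 produces outcome-dependent missing data in symptom reports, GAD-7, visit samples and adverse events. At the planning rates 15% of placebo and 7.5% of HCQ subjects would be closed within four weeks (45 against 22.5); at the lower placebo rates considered in Section 8.1 the imbalance shrinks to 30 against 15 and 15 against 7.5. These figures assume an equal split of 600 and the planned halving of risk. With no drug effect the expected counts would be equal, but the missing data would still be concentrated in the sickest subjects.

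Loss of hospitalization, ICU or death endpoints is not shown. For these, and for a Covid-19 admission that follows an earlier admission for another cause, the defect is a missing statement.

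**What to change.** Reconcile Section 3.2 with Sections 3.3, 4.7, 6.3, 7.2.1, 7.3.3 and 13 by amendment:

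- In Section 3.2, remove the conclusion of participation at hospitalization. The provisions on study medication and on opening the code are not at issue here.
- State that outcome assessments (where feasible) and record and register follow-up continue after any admission, for every randomized subject who has not withdrawn consent. The 6-month collection stays subject to consent, as already planned. The investigator's existing right to withdraw a subject is unaffected.
- State that a Covid-19 admission within four weeks of entry counts for the primary endpoint even after an earlier admission for another cause.
- Give one end point for adverse event recording in Section 7.3.3.
- Flag patient-reported data collected after the code is opened.

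How admission or death is scored in the symptom analysis can be left to the SAP.

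The cost is a short amendment and a few extra contacts; the visits, calls and registers are already planned. The downside is that some patient-reported data after admission may be unblinded.

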## 2.4 Primary endpoint

The primary endpoint of the study is:

- number of hospitalizations due to Covid-19 infection within four weeks of entry into the study; the study hypothesis is that treatment with HCQ will reduce the risk of hospitalization because of Covid-19 infection, and the sample size estimate of the study is based on the need to test this hypothesis.

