### 8.2.1 Statistical Analysis Plan

Detailed statistical analysis information will be provided in the SAP before database lock.

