### 8.2.3 Data sets to be analyzed

A subject classification document including a list of protocol deviations with a clinical classification of the deviations and the definition of the analysis datasets will be prepared and approved after database lock before opening of the randomization code.

Three main analysis data sets will be constructed. The intention-to-treat (ITT) data set will include all enrolled subjects. The safety data set will consist of all subjects having received at least one dose of study medication. The per-protocol (PP) dataset including all subjects with SARS-CoV-2 PCR-confirmed Covid-19 infection who received at least four days of treatment with study medication and for whom evaluable outcome data are available.

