## 9 QUALITY CONTROL AND QUALITY ASSURANCE

During the clinical execution of the trial, the principles of GCP are followed throughout the study. For data management and statistics, the standard operating procedures of 4Pharma are followed.

The analyses of safety laboratory assessments will be performed at the laboratory of SataDiag. The analysis of HCQ concentrations in whole blood samples is planned to be performed at the Bioanalytical Laboratory of the University of Turku, Institute of Biomedicine. Diagnostic PCR testing will be carried out at SataDiag and antibody testing from serum will be performed by collaborating researchers at TYKSLAB and the University of Turku. Optional pharmacogenetic testing for drug metabolizing enzymes will be carried out by Abomics Ltd. HLA haplotyping will be performed by TYKSLAB, the accredited hospital laboratory of Turku University Hospital. Laboratory quality certificates will be available.

The study will be monitored by Turku Clinical Research Centre (TurkuCRC). The monitor is allowed to monitor the study as frequently as necessary to ensure that the data recording and protocol adherence are satisfactory. The eCRFs and related source data will be reviewed in sufficient detail.

A curriculum vitae in English will be obtained from all investigators who sign the protocol and from other relevant persons.

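### The code is opened for every primary-endpoint case, so the attribution of an admission to Covid-19 is not protected from knowledge of the arm, and the blinding statements in 3.2 and 8.2.3 cannot hold for these subjects

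*Protocol*

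**What the plan says.** The primary endpoint in section 2.4 is the "number of hospitalizations due to Covid-19 infection within four weeks of entry into the study". Section 7.2.1 determines it, with Covid-19 ICU episodes and Covid-19 deaths, by evaluating patient records and register data.

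Section 3.2 describes the trial as double-blind, with participants and study personnel kept unaware of allocation. It limits unblinding by the investigator to cases of medical need. A separate rule then applies to any death or hospitalization: "the treatment code of that subject will be opened by the Medical Lead of the study". That rule carries no test of need. Two recipients are named:

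- the treating hospital: "For hospitalized subjects, this information will be communicated to the hospital in charge of the" patient's further care;
- the Steering Committee (SC): "De-identified unblinded information on deaths and hospitalizations will also be provided to the SC".

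The Synopsis (Number of Subjects) and section 10 add that the SC and the data management (DM) provider follow all hospitalizations and deaths unblinded.

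On classification, section 8.2.3 says that the document listing deviations and defining the analysis sets "will be prepared and approved after database lock before opening of the randomization code". On the analysis plan, section 8.2.1 says: "Detailed statistical analysis information will be provided in the SAP before database lock". Section 9 says: "For data management and statistics, the standard operating procedures of 4Pharma are followed". Section 11.1 identifies that same company as the DM provider.

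**The concern.** The endpoint is cause-specific. Someone must judge whether an admission was caused by Covid-19 or by something else, including a drug effect. Knowing the arm can sway that judgement, because a drug explanation is open only for a subject known to be on HCQ. If such admissions are classed as drug-related more readily, they leave the primary count in one arm only. The Covid-19 ICU and death endpoints are exposed in the same way, and most of those events follow an admission, so they arise once the hospital may already know the arm.

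The wording is also inconsistent. Study personnel cannot all remain blind if the Medical Lead and the DM provider work with allocations for every event. Nor can classification precede the opening of a code that has already been opened for every subject with an event.

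**Working it through.** **1. Is every primary case unblinded?** A primary case is a hospitalization (2.4). Every hospitalization triggers a code-break (3.2). So all primary cases are unblinded while the trial runs. Subjects who survive and are never admitted stay masked, apart from emergency code-breaks.

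**2. Is the attribution protected?** Section 7.2.1 uses patient records and registers. For an admitted subject these include records kept by the hospital that has been told the arm. No section names the person who attributes cause, keeps that person from the allocation, or requires the attribution before the code is opened. The supportable statement is that blinding is not protected, not that it is known to be broken.

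**3. Section 8.2.3 against section 3.2.** One places approval of the classification after database lock and before code opening. The other opens the code at each event. For hospitalized or deceased subjects both cannot hold. Per-protocol membership also depends partly on judgement: whether outcome data are evaluable, and how deviations are classified clinically.

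**4. The plan's sample size, for scale.** Inputs from section 8.1 and the Synopsis: 15% against 7.5%, two-sided 0.05, 80% power. With mean rate 0.1125:

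n = [1.960·√(2·0.1125·0.8875) + 0.8416·√(0.15·0.85 + 0.075·0.925)]² / 0.075² = 277.5, so 278 per group.

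The stated 278 is reproduced, as are 435 (10% rate) and 906 (5% rate).

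**5. Number of cases.**

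| Per group | Planned effect | No effect (15% in both arms) |
|---|---|---|
| 278 | 41.7 + 20.9 = about 63 | about 83 |
| 300 | 45 + 22.5 = about 68 | 90 |

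**6. What biased attribution could do (assumed shares).** Let the true rate be p in both arms. A share m of HCQ-arm cases is recoded as not due to Covid-19, so the observed HCQ rate is p(1 − m). The test is the pooled two-proportion z test, standing in for an unadjusted logistic regression. The table gives P(z > 1.96 in favour of HCQ) at 300 per arm, by exact binomial enumeration.

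| m | p = 15% (cases moved) | p = 10% | p = 5% (cases moved) |
|---|---|---|---|
| 0 | 2.5% (0) | 2.5% | 2.5% (0) |
| 5% | 4.5% (2.25) | 4.0% | 3.4% (0.75) |
| 10% | 7.6% (4.5) | 6.2% | 4.7% (1.5) |
| 20% | 18.9% (9) | 13.6% | 8.4% (3) |
| 30% | 38.2% (13.5) | 26.3% | 14.5% (4.5) |

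**7. Sensitivity at the margin.** With 278 per group, 42 against 27 cases gives p = 0.054, and 42 against 26 gives p = 0.038 (uncorrected chi-square). Near the threshold, one attribution can change the conclusion.

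**The case against.** Several points on the other side stand.

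- **Disclosure and timing.** The unblinding is stated openly. It follows the admission, so the decision to admit can still be made blind.
- **Size.** The documents give no basis for any particular share of recoded cases. All subjects are PCR-positive, and a long QTc interval and QT-prolonging drugs are exclusions, so admissions that could plausibly be blamed on the drug should be a minority. Recoding a truly drug-caused admission is correct classification. At small shares or low event rates the inflation is modest.
- **Existing check.** All-cause hospitalization and mortality within six months are secondary endpoints from the same registers and need no attribution. They cover a much longer window, however, and the post-study part is limited to consenting subjects.

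Two stronger readings are tempting but unsupported.

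- **The SAP and model choice are made with the arms known.** Section 8.2.1 fixes only timing and makes no claim about blindness. One company's procedures cover both data management and statistics, but that does not show the statisticians see allocations. A firewall is neither stated nor excluded. Section 8.2.6 already fixes logistic regression and analysis in both the ITT and PP sets, and PP membership is mostly rule-based.
- **The treatment-related adverse event endpoints are equally exposed.** Section 7.3.3 makes severity and causality the first decision, gives it to the investigator, and requires serious events to be reported within 24 hours. The investigator is not a named recipient of the code opened by the Medical Lead. The order is not made explicit, but the text points to an assessment made without the allocation.

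Neither the modest figures nor these limits remove the unprotected primary attribution or the contradiction in section 8.2.3.

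**Conclusion.** The point holds for the attribution of the primary endpoint, and for Covid-19 ICU episodes and deaths: the arm is opened for every case, and nothing protects the cause judgement from it. Section 8.2.3 is untrue as written for every hospitalized or deceased subject, and the general blinding statement in section 3.2 conflicts with the unblinded follow-up described in the Synopsis and section 10. The SAP's timing is a lesser matter, resting on an unstated separation of staff within one company.

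The size is illustrative. It assumes no true effect, one-directional recoding and an unadjusted test, and spans 3.4% to 38.2% false benefit against a nominal 2.5% across the shares and rates shown. The case for acting rests on the text rather than on any one of these figures. Attribution bias cannot be repaired after database lock, and prevention is cheap.

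**What to change.** Leave the code-break for care as it is; whether the hospital should be told is not a question for this point.

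1. Have the site investigator, who is not given the allocation, enter the admission date and a yes/no attribution to Covid-19 in the eCRF before the code is opened. In an emergency, have staff not told the result enter it within a set time. State that this entry, not later coding by the treating hospital, defines the primary endpoint. Without that statement the hospital's records could still decide the case.
2. Pre-specify all-cause hospitalization or death within four weeks as a sensitivity analysis, from the registers already used for the six-month all-cause endpoints. If the SAP, not shown here, already has this, confirm it.
3. Reconcile the Synopsis with sections 3.2, 8.2.3 and 10. Have the deviation and PP classification and the SAP finalized by staff without access to any subject's allocation, and reword section 8.2.3 to say so instead of stating that no code has been opened.

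Cost: amendment wording, an ordered eCRF field, a firewall at the DM provider and an earlier SAP. No new data or study procedure is needed.
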